## Abstract

**Background:**

African Americans have the highest incidence and mortality and are less likely than whites to have been screened for colorectal cancer (CRC). Many interventions have been shown to increase CRC screening in research settings, but few have been evaluated specifically for use in African-American communities in real world settings. This study aims to identify the most efficacious approach to disseminate an evidence-based intervention in promoting colorectal screening in African Americans and to identify the factors associated with its efficacy.

**Methods/design:**

In this study, investigators will recruit 20 community coalitions and 7,200 African-Americans age 50 to 74 to test passive and active approaches to disseminating the Educational Program to Increase Colorectal Cancer Screening (EPICS); to measure the extent to which EPICS is accepted and the fidelity of implementation in various settings and to estimate the potential translatability and public health impact of EPICS. This four-arm cluster randomized trial compares the following implementation strategies: passive arms, (web access to facilitator training materials and toolkits without technical assistance (TA) and (web access, but with technical assistance (TA); active arms, (in-person access to facilitator training materials and toolkits without TA and (in-person access with TA). Primary outcome measures are the reach (the proportion of representative community coalitions and individuals participating) and efficacy (post-intervention changes in CRC screening rates). Secondary outcomes include adoption (percentage of community coalitions implementing the EPICS sessions) and implementation (quality and consistency of the intervention delivery). The extent to which community coalitions continue to implement EPICS post-implementation (maintenance) will also be measured. Cost-effectiveness analysis will be conducted.

**Discussion:**

Implementing EPICS in partnership with community coalitions, we hypothesized, will result in more rapid adoption than traditional top-down approaches, and resulting changes in community CRC screening practices are more likely to be sustainable over time. With its national reach, this study has the potential to enhance our understanding of barriers and enablers to the uptake of educational programs aimed at eliminating cancer disparities.

**Trial registration:**

http://www.ClinicalTrials.gov NCT01805622

## Background

Colorectal cancer (CRC) is the third most commonly diagnosed cancer and the second leading cause of cancer death in the United States (US) [1]. The American Cancer Society (ACS) estimates that over 142,820 people will be diagnosed with CRC and over 50,830 people will die from this disease in 2013 [1]. The most frequently recommended screening tests for CRC include annual fecal occult blood testing (FOBT) or colonoscopy every ten years. Alternative screening tests are sometimes used: sigmoidoscopy every five years (combined with annual FOBT), or double-contrast barium enema every five years. Fecal DNA and computed colonoscopy are available, but still considered investigational by many third-party payers. Endoscopy is not only a mode of early detection (secondary prevention); it also serves as primary prevention when a precancerous polyp is removed. CRC screening is substantially underutilized in the US, with only about 55% of those for whom screening is recommended (persons 50 years and older) having been screened with the recommended frequency [2].

Factors associated with the use of CRC screening may be characterized as patient-related, physician-related, or system-related. Patient-related factors include having insurance coverage, a source of medical care, and higher education and income. A number of knowledge, belief, and attitudinal factors also play an important role [3]. A screening recommendation from a physician is the only physician-related factor. System-related factors include electronic medical records, ancillary personnel who can provide follow-up and patient navigators [2]. African Americans have by far the highest CRC incidence and mortality rates of any racial/ethnic group. African American mortality is 50% higher than the second-highest group (white), and more than double that of the group with the lowest mortality (Asian/Pacific Islander) [4]. Likely related to the mortality disparity is the disparity in CRC screening. Similar percentages of African Americans (23.8%) and whites (21.3%) age 50 years and older have had an FOBT within the last two years, but whites (64.0%) are substantially more likely to have had endoscopy (ever) than African Americans (58.6%) (2008 data) [5].

Subsequent to CCSIT, we entered into a partnership with the local health department (Fulton County Department of Health and Wellness) and local Office on Aging to put EPICS into practice in the county’s 15 senior citizen centers. At the urging of the health department’s health educators, the number of sessions in the intervention was shortened to three. In the practice demonstration, 331 mostly African-American men and women 50 years and older who had never been screened for CRC, or who were not up-to-date, received the intervention. At three-month follow-up, 37.3% had been screened; another 33.8% stated that they had appointments for screening or intended to get an appointment [9]. It is unusual for an intervention to perform as well in practice (effectiveness) as in the research setting (efficacy). However, EPICS performed at least as well in practice as it did in the community intervention trial, even discounting participants who had not yet been screened, but stated that they intended to do so or had an appointment [9].

Based on initial success in a ‘real world’ setting, we then initiated a state-wide EPICS dissemination and implementation project. To reach most of the state, we partnered with five of the six Regional Cancer Coalitions of Georgia (RCCG) and their parent body, the Georgia Cancer Coalition (GCC). We trained facilitators in each of the regional coalitions and in 12 hospital-based American College of Surgeon-accredited cancer programs. We also gained firsthand knowledge of dissemination and implementation processes from the state practice demonstration that will be used in the proposed project, including strategies for: engaging decision makers and stakeholders; developing, packaging, and enhancing the intervention toolkit; designing and improving facilitator training and certification; developing an implementation protocol; establishing quality assurance measures; and enhancing technical assistance for successful efficacy-to-effectiveness translation [10].

### Goals and aims

The overall goals of this research are to identify the most efficacious approach to disseminating EPICS and to identify the factors associated with its effectiveness.

Key aims are to:

1. Test passive and active approaches to disseminating EPICS.

2. Measure the extent to which EPICS is accepted by community coalitions and the fidelity of implementation in various settings.

3. Estimate the potential for translation and the public health impact of EPICS.

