### Power analysis

Power calculations were performed to further justify our proposed sample size. All of these assume a sample size of 1,800 per study arm, a significance level of 5% (*i.e.* alpha = 0.05), and a two-sided two-group chi-square test of proportions. Calculations were performed using nQuery Advisor, version 7. These are performed for hypothesis one (H1) and hypothesis three (H3); hypothesis two (H2) is qualitative, so power calculations do not apply. For H1, we anticipate that there will be 25%, 33%, and 50% greater participant enrollment with the Web + TA arm, IP arm, and IP + TA arm, respectively, when compared to the passive web-based-only arm (based on our prior experience with community coalition based studies). Comparisons of any of these proportions to any proportion that is obtained for the passive web-based arm (for example, 5%, 10%, or 20%) will result in greater than 99% power to detect differences in the proportions as being statistically significant. For H3, we can obtain estimates of cancer knowledge change over time (pre-intervention to post-intervention percentages with the correct response) for a small group education cohort and a control cohort from Blumenthal, Smith *et al.*[6]. These estimates include changes of 34.8 (71-36) and 15.5 (55.2-39) for a CRC perceived risk question, and 22.9 (92.9–70) and 13.1 (88.5–75.for a CRC screening question. Assuming that we observe similar changes in our study participants for active and passive arms, we will have greater than 99% power to detect differences in the proportions as being statistically significant.

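### The goal is to find the most efficacious of the dissemination approaches, but no stated test or power separates web + TA, in-person and in-person + TA

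*Protocol article*

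**What the plan says.** - **Goal.** Goals and aims states the overall goal as to "identify the most efficacious approach to disseminating EPICS". The Abstract says the same: "This study aims to identify the most efficacious approach to disseminate an evidence-based intervention". The first aim is "Test passive and active approaches to disseminating EPICS".
- **Arms.** The Abstract (Methods/design) and Trial design describe four strategies: web access (WA), WA+TA, IP and IP+TA. Twenty coalitions are randomized.
- **Power for hypothesis one.** The Power analysis section anticipates "25%, 33%, and 50% greater participant enrollment with the Web + TA arm, IP arm, and IP + TA arm, respectively", all relative to web-only, and claims more than 99% power for "Comparisons of any of these proportions to any proportion that is obtained for the passive web-based arm", with 5%, 10% and 20% as example web-only rates. On the sample size it says: "All of these assume a sample size of 1,800 per study arm". The test is "a two-sided two-group chi-square test of proportions" at the 5% level.
- **Active against passive.** This contrast is hypothesis one itself (Hypotheses). It is also the effectiveness comparison by setting (Effectiveness) and the basis of the power statement for hypothesis three (Power analysis).
- **All four strategies.** The Cost-effectiveness analysis section compares costs and outcomes of the four, removes dominated ones and forms incremental ratios against the next less effective strategy.

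**The concern.** To name a best strategy, the leading arm has to be separated from its nearest rivals. Neither stated family of contrasts does that:

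- Three results against web-only can all be positive and still leave WA+TA, IP and IP+TA unranked.
- Active against passive pools IP with IP+TA and WA with WA+TA. Each pool holds one arm with TA and one without, so the contrast says nothing about whether TA adds to in-person delivery. Yet the Theoretical framework section lists establishing the role of TA as a task for that same comparison.

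The cost-effectiveness ordering inherits the gap. If two strategies are close, chance can decide which counts as more effective, and that order then feeds into dominance and the incremental ratios. The sensitivity analyses described there vary inputs such as wages and session size, and no precision is stated for the order itself.

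At stake is the headline conclusion. The claim of more than 99% power could be taken as support for identifying a best strategy, which it does not cover.

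**Working it through.** **Inputs (Sample size calculation and Power analysis).** n = 1,800 per arm; two-sided 5%; web-only rate b = 5, 10 or 20%; anticipated gains of 25%, 33% and 50%; ICC 0.0911; stated design effect 1.2754; 30 groups × 12 completers = 360 per coalition; 20/4 = 5 coalitions per arm.

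**Formula.** With d = |p1 − p2|, s0 = √(2p̄(1−p̄)/n) and s1 = √((p1(1−p1) + p2(1−p2))/n):

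power = Φ((d − 1.96·s0)/s1) + Φ((−d − 1.96·s0)/s1).

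**Step 1: reproduce the article's figure (each arm against web-only).** The wording allows three scales.

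| Reading | WA+TA / IP / IP+TA against web-only | More than 99% reproduced? |
|---|---|---|
| Relative (b×1.25, 1.33, 1.50) | b=5%: 37/56/87%; b=10%: 66/87/99.5%; b=20%: 95/99.7/100% | No |
| Percentage points (b+25, 33, 50) | about 100% throughout | Yes |
| Absolute rates (25, 33, 50%) | about 100%, except 94.9% for 25% v 20% | All but one |

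**Step 2: contrasts among the other three arms, no clustering.** Worked case, relative reading, b = 10%, IP+TA v IP: p = 0.150 and 0.133, d = 0.017, s0 = 0.01162, s1 = 0.01161. Then (0.017 − 1.96×0.01162)/0.01161 = −0.497 and power = 31%.

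| Contrast | Relative, b = 5/10/20% | Percentage points or absolute |
|---|---|---|
| IP v WA+TA | 8/11/20% | at least 99.8% |
| IP+TA v IP | 17/31/62% | about 100% |
| IP+TA v WA+TA | 32/59/92% | about 100% |

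**Step 3: allow for clustering.**

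- *Stated design effect.* n = 1,800/1.2754 = 1,411 per arm. Relative reading: IP+TA v IP falls to 14/25/52%. Percentage-point or absolute reading: at least 98.9% for every pair.
- *Coalition as cluster (assumption: ICC 0.0911 applies to 360 people per coalition).* Design effect = 1 + 359×0.0911 = 33.7, so n = 1,800/33.7 ≈ 53 per arm. Percentage-point or absolute reading: about 13-15% for IP v WA+TA, 42-44% for IP+TA v IP and 74-77% for IP+TA v WA+TA. Relative reading: below 10% for every pair.

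**Step 4: what the planned pooled contrast offers.** Active against passive, 3,600 v 3,600, relative reading, unclustered: 71/96/100%. It is better powered, but it answers a different question.

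**The case against.** - **The goal may mean passive against active.** The first aim, directly below the goal, uses approaches in that sense, and that contrast is planned. This is a fair reading, and it is why active against passive should stay. But the Abstract says that the trial compares four strategies, and the cost-effectiveness section ranks all four.
- **A reader might infer that web-only contrasts are the only arm comparisons planned or powered.** The document does not support that: active against passive is planned for enrollment and screening and is powered for hypothesis three.
- **A reader might infer that the close pairs have 8-62% power whatever is assumed.** That range needs relative increases. Relative is the plain sense of the wording, but on that reading the article's own power claim fails too. The percentage-point reading, which reproduces the claim throughout, gives near-certain power before clustering.
- **The figures concern enrollment.** The Abstract equates efficacy with change in screening rates, so these numbers do not measure the ability to rank strategies on screening. Also, 1,800 per arm counts expected completers, while Reach is divided by eligible people in the settings. Both limits stand.
- **The large design effect is an assumption.** The ICC comes from the earlier trial, and the stated design effect implies a cluster size of about 4 (1 + 0.2754/0.0911). This stands, so the coalition-level figures are conditional.
- **An analysis plan could add pairwise contrasts.** It could. The point here is that the article itself states the goal, the contrasts and the power, and these do not match. Nor does any section say that the arm furthest above web-only will be declared best, so that rule should not be attributed to the plan.

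**Conclusion.** The mismatch holds in a limited form. The article's stated tests and power cover each arm against web-only and active against passive. The four-way cost-effectiveness ordering has no stated test or precision. Nothing stated separates WA+TA, IP and IP+TA, so the planned contrasts cannot show which strategy is best.

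How weak the missing contrasts would be cannot be fixed from the article, because the effect scale is not explicit. For enrollment, power for the two closest pairs runs from 8-62% (relative, unclustered) to at least 99.8% (percentage points or absolute, unclustered). On the latter readings it drops to 13-44% if ICC 0.0911 holds at coalition level. Whether the contrasts are missing does not depend on any of these readings. This is a cheap improvement that changes what the trial can conclude. It does not invalidate the active-against-passive comparison.

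**What to change.** 1. Keep active against passive.
2. Add the pairwise contrasts among all four arms or, equivalently for a 2×2 layout, delivery mode, TA and their interaction. Analyse them at coalition level, for both enrollment and screening, with simultaneous confidence intervals.
3. When no single strategy separates, report the set not distinguishable from the best. The exact decision rule is the team's choice. Requiring an interval that excludes zero against every rival is one option among several, and it should be fixed in advance.
4. Say whether the 25%, 33% and 50% are relative increases, percentage points or absolute rates. State the power for the added contrasts on that scale, and confine the claim of more than 99% to contrasts that it covers.

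The cost is wording and a few extra contrasts on data already being collected, with no added participants. The downside is a less favourable stated power and possibly a best set in place of one winner.

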## Methods/design

### Ethical approval and informed consent

The Institutional Review Board (IRB) of the Morehouse School of Medicine has approved our research plan. Informed consent will be obtained for all study participants: community coalition leaders, EPICS facilitators, and individual participants. The study is registered with ClinicalTrials.gov as NCT01805622.

### Community coalitions

The community coalitions that will serve as clusters in the EPICS cRCT are part of the National Black Leadership Initiative on Cancer (NBLIC), a network that was founded in 1987 and have primarily engaged in community education efforts; this history has been described elsewhere [11]. The coalitions include individuals from academia, business, health care, non-profit organizations, and other community stakeholders. Twenty of the 33 NBLIC community coalitions will be randomized as clusters in the EPICS cRCT. In developing this project, we executed Memoranda of Understanding (MOU) between the coalitions and Morehouse School of Medicine; recruited research sites and surveyed the community coalitions’ organizational characteristics.

### Trial design

This study is a four-arm, cluster randomized controlled trial (cRCT). Figure 1 depicts information from four stages of the EPICS cRCT (enrollment, intervention allocation, follow-up, and analysis) based on the recommended flow of parallel group randomized trials [12].

**Figure 1 F1:**
[figure not shown]
CONSORT flow diagram for EPICS cRCT.

Randomization at the organizational (community coalition) level has been chosen because this will minimize contamination that may occur if individual participants are randomized. In utilizing cluster randomization, we will focus on community coalitions as the cluster for all study arms, with individuals within their target settings as the secondary unit. We will ensure balance in all four study arms by ordering them into groups based on the total number participating. A computer program generating random numbers between 1 and *n* will be used to assign community coalitions to one of four conditions: web access (WA) to facilitator training materials and toolkits without technical assistance (TA); the same as 1, but with technical assistance (TA); in-person access (IP) to facilitator training materials and toolkits without TA; and in-person access to facilitator training materials and toolkits with TA. Our multilevel approach (*e.g.*, cluster, setting, and individual) promotes widespread dissemination [13]. Community coalitions will be allocated to one of the four arms and informed consent will be obtained from community coalition members and from individual participants.

### Toolkit

The EPICS toolkit is a package that includes facilitator training materials (manual, workshop agenda, and certificates); implementation protocol; EPICS curriculum; individual/participant educational materials; and individual/participant incentives. The toolkit was developed and pilot tested during the local and state practice demonstrations. Community coalitions randomized to passive dissemination arms will access all toolkit components except participant incentives via the web. Those randomized to active dissemination will receive all toolkit components via in-person delivery. In the case of individual/participant incentives, delivery will be via US Postal Service for community coalitions in all dissemination arms.

1. Facilitator training: Consistent with principles of Adult Learning Theory, the EPICS facilitator training workshop is skill-based, highly participatory, and provides learners with immediate opportunities to apply new skills and information [14]. A user-friendly Facilitator Training Manual has been developed and tested. The one-and-one-half-day facilitator training workshop introduces basic vocabulary, concepts, and methods of community-based cancer control and instructional strategies for African Americans of varying health literacy. Each community coalition will identify a minimum of five members, in addition to a leader, to complete facilitator training. Community coalitions randomized to passive dissemination arms will download training materials from the National Cancer Institute’s Research Tested Intervention Programs (RTIPs) website (http://rtips.cancer.gov/rtips/index.do) and conduct the training themselves, while those in active dissemination arms will be trained by EPICS developers. The facilitator training workshop consists of three modules that address: principles knowledge (*e.g.*, conceptual framework, intervention overview, and local/statewide demonstration projects); procedural knowledge (*e.g.*, how to implement the three EPICS sessions); and practical knowledge (*e.g.*, how to market the programs and complete the EPICS assessments and measures).

2. Implementation Protocol: We also developed and tested a protocol similar to that used in the original CCSIT study and converted it into non-academic language. This 12-step protocol includes procedures to: recruit community partners; schedule sessions; market the program; recruit participants; prepare for the sessions; sort the toolkit; assign facilitators; deliver the sessions; identify ‘completers’ (participants attending all three intervention sessions); monitor screening; submit reports; and get technical assistance.

3. EPICS Curriculum: Individual participants in all study arms will complete three small group educational sessions. These sessions, each approximately one-hour in length, will be conducted the same day/time of the week for three consecutive weeks. This schedule will be formulated by NBLIC community coalitions in conversation with intervention settings at a time likely to solicit the greatest participation.

4. Individual/participant CRC educational materials include three session-specific brochures, CDC consumer education materials, including: Get Smart in Your Family Dinner; Get Smart as You Shop; and CRC Facts on Screening.

5. Individual/participant incentives such as a cookbook, water bottles, shopping bag, and similar items are distributed to individuals completing all three EPICS sessions.

### Churches, clinical partners, and community sites

Three settings with congregants, patients or clients, aged 50 to 74 years, will participate in the study: churches, including Protestant and Catholic churches and other faith-based institutions; clinical cites, including health departments, community health centers, hospitals and similar healthcare providers; and community cites*,* including senior citizen centers, assisted living facilities, and community centers. NBLIC community coalitions, based on their relationship and history with these community institutions, will work closely with the leaders of these organizations to assist in individual participant recruitment.

